## Abstract

**Background:**

A key concern for people with chronic pain is experiencing increased pain and/or re-injury. Consequently, individuals with chronic pain can develop a maladaptive fear of movement that leads to adverse functional consequences. A primary goal of chronic pain rehabilitation is re-engagement in feared movements through exposure. This is often challenging since safe movement can be uncomfortable. Virtual environments provide a promising opportunity to safely and gradually expose Veterans to movements that are avoided in the real world. The current study will utilize multiple virtual reality (VR) applications (APPs) of varying the intensity levels ranging from passive distraction from pain to active exposure to feared movement. The primary aims of this pilot are to examine VR as an adjunctive nonpharmacological intervention to assist with the adoption and implementation of skills to decrease fear of movement and increase overall functioning among Veterans with chronic pain. Second, to build a hierarchy of VR APPs to assist in gradual exposure to feared movements.

**Methods:**

This study will be conducted in the Chronic Pain Rehabilitation Program (CPRP) at the James A. Haley Veterans Hospital, a unique inpatient program within the VA system. Participants will include up to 20 Veterans who receive a VR intervention as part of their physical therapy. A rating form containing qualitative and quantitative experiences will be administered following each VR session to assess feasibility and to provide descriptive information for the proposed hierarchy. Effect sizes will be calculated from intake and discharge measures for the primary outcome fear of movement and secondary pain and functional outcomes.

**Discussion:**

This study will inform the feasibility of a randomized controlled trial examining the clinical utility of using VR to reduce fear of movement and increase function among Veterans with chronic pain. VR has the advantage of being easily implemented both within VA healthcare settings as well as in Veterans’ own residences, where engagement in ongoing self-management approaches is often most challenging. Presumably, VR that is matched to patient needs, progresses in intensity, immerses Veterans in the applications, and is perceived positively by Veterans, will result in positive functional outcomes.

## Background

Pain is among the most costly disorders treated in Department of Veterans Affairs (VA) settings [1]. Over five million Veterans were diagnosed with at least one musculoskeletal disorder from 2001 to 2011, nearly half of whom reported moderate-to-severe pain [2]. The treatment of pain was established as a VA priority in 1998 [3], but in recent years, pain management has received more attention due to national concerns regarding opioid overdose, addiction, and high-profile adverse events [4]. Given this burden, the Centers for Disease Control and Prevention [4] and other national organizations [5] have recommended non-pharmacological approaches as the preferred treatments for chronic non-cancer pain.

### Fear of movement

A key concern for people with chronic pain, defined as pain persisting longer than 3 months [6], is experiencing increased pain or (re) injury [7]. As a result, individuals often develop kinesiophobia, a fear of movement [7]. Kinesiophobia can be helpful in acute pain which lasts less than 3 months [6], but maladaptive in chronic pain, as it leads to adverse functional consequences [7]. A primary goal of chronic pain rehabilitation is re-engagement in feared movements through exposure. However, this is often challenging since safe movement can be physically and emotionally uncomfortable [8].

### Virtual reality

Virtual reality (VR) can be defined as “computer-generated simulations of three-dimensional objects or environments with seemingly real, direct, or physical user interaction” (pg. 34) [9]. Today’s virtual technologies use the computer and wearable devices to give the user the illusion of being immersed or present in a non-physical world [10, 11]. VR can serve as an adjunctive method in evidence-based interventions to assist with the delivery and adoption of self-management skills [11–13]. When VR that is matched to patient level of functioning progresses in intensity, immerses people in the applications, and is perceived positively, it can contribute to improved fear of movement and disability [12, 13]. To date, VR research [11–13] has prominently focused on two cognitive behavioral therapy [8] techniques, distraction from and exposure to pain.

### Virtual reality and pain distraction

Evidence supports the use of VR to attenuate pain with the majority of evidence to date aimed at treating acute pain. A rapid evidence assessment of immersive VR for acute pain management (17 studies, 337 patients) found strong evidence for immediate and short-term pain reduction, as well as moderate evidence for short-term analgesic effects on physical function [11]. Distraction-focused treatments (e.g., guided imagery, relaxation training) are the most commonly researched VR-administered interventions for acute pain relief [11, 14]. Distraction therapy is based on the assumption that humans have finite attentional resources [8, 15]. VR distraction is hypothesized to consume attention leaving less cognitive capacity for processing pain [15] and fear of movement [13]. A recent controlled trial conducted in an inpatient acute pain care setting demonstrated reduced pain scores among patients playing a “medium-intensity” pain distraction VR application (APP) compared to a televised high-definition nature video [16]. Pilot work suggests that relaxation using VR may be associated with reduced pain intensity among people with chronic pain [17].

### Virtual reality and exposure therapy for pain

In contrast to pain distraction, exposure therapy *focuses attention* on the fearful stimulus and inducing a feeling of “being there” [18, 19]. To be effective, exposure therapies should be graded, motivating, and related to real-life functional activities [14, 20]. A randomized study found that integrating exposure via guided virtual walking into physical therapy resulted in a significant decrease in fear of movement and pain intensity when compared to physical therapy without VR [21]. A feasibility study found high acceptability ratings of a virtual dodgeball intervention to influence lumbar flexion for people with chronic low back pain and pain-related fear [22]. No participants withdrew from the study and no adverse events or increased medication use was reported [22]. This evidence supports using VR as an adjunctive therapeutic delivery method for reducing fear of movement among people with chronic pain [21, 22].

### Hierarchy from distraction to exposure

It has been argued that distraction from pain-related thoughts and emotions can promote avoidance of factors contributing to the development and maintenance of chronic pain [12, 13]. This can undermine the effectiveness of distraction-only VR therapies among chronic pain populations who have a greater need for rehabilitation than immediate relief [12, 23]. We have conceptualized a two-dimensional hierarchy for movement and intensity of stimulation for people with chronic pain. The hierarchy will range from low-intensity pain distraction to more “interactive” graded exposure techniques within the same VR-assisted intervention (e.g., sitting passively in a chair during guided meditation to standing and using body movement to engage in virtual activities such as painting).

### Current study

The proposed project is informed by the Fear-Avoidance Model of Chronic Pain [7] and assumes that as people gradually confront feared activities through VR, maladaptive pain beliefs are challenged and fear responses are extinguished [14, 24]. Both distraction [22] and exposure [21] could be beneficial for improving fear of movement among people with chronic pain. Still, studies typically examine these methods independently despite the former being inherent during VR utilization [14]. This will be the first known study that will investigate the use of immersive VR across a distraction to exposure spectrum as an adjunct strategy for chronic pain management in a sample of US Veterans.

## Aims and objective

The objective of this study is to establish feasibility for a future randomized controlled trial (RCT) that will test the effectiveness of VR as a treatment adjunct for chronic pain management and aim to validate the proposed hierarchy. The primary aims are as follows:

Aim 1: Describe the individual Veteran trajectories and APP intensity ratings on the proposed distraction-to-exposure hierarchy.
RQ 1.1: How many different trajectory patterns emerge as Veterans progress across the intensity levels of the distraction-to-exposure hierarchy?RQ 1.2: How do Veterans rate the intensity of the VR APPs?

Aim 2: Estimate the within-subjects effect size and 95% confidence interval (CI) associated with changes in fear of movement and secondary outcomes to provide insight into the likely magnitude of effect associated with the VR intervention.
RQ 2.1: What is the estimated within-subjects effect size and 95% CI for changes in the primary outcome, fear of movement, from baseline to post-test following the VR intervention?RQ 2.2: What is the estimated within-subjects effect size and 95% CI in *common* feared movements from baseline to post-test following the VR intervention?RQ 2.3: What are the within-subjects effect sizes and 95% CIs for changes for the secondary outcomes of pain intensity, pain interference, pain catastrophizing, pain-related functioning, and negative affect from baseline to post-test following the VR intervention?RQ 2.4: What proportion of Veterans experience clinically meaningful change for the following outcomes: common feared movements, pain intensity, pain catastrophizing, pain-related functioning, and negative affect?

Aim 3: Pilot test this protocol to assess the feasibility of VR use to plan for a future randomized controlled trial.
RQ 3.1: How do Veteran users describe their experiences with VR during this study?RQ 3.2: What are the identified barriers and facilitators of VR use?RQ 3.3: What is the estimated compliance (percentage of sessions attempted, completed) with VR?

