## Methods

### Study setting

The CPRP at the James A. Haley Veterans Hospital is a 19-day residential chronic pain treatment program. The interdisciplinary treatment provided in the CPRP utilizes a cognitive behavioral treatment approach that targets the physical and psychological impact of chronic pain. The CPRP is the sole inpatient chronic pain program within the VA system, and its attendees are Veterans referred system-wide.

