### Design

A type 1 hybrid design will be used to blend clinical effectiveness and implementation research to accelerate the proposed VR intervention into practice. Primary and secondary outcomes (Aim 2) will be assessed using a within-subjects pretest-posttest design. Qualitative pre-implementation data will be collected following each VR session. The VR intervention will be implemented as an adjunct part of graded exposure physical therapy (PT) sessions in the CPRP. For each session, participants will be assigned to use one of two VR head-mounted displays (HMD: Oculus Rift, Gear VR). VR assignment will be balanced secondary to equipment availability. Specifically, participants will participate in two sessions of Gear VR [27] for each session of Oculus Rift [28].

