### Procedures

At CPRP admission, licensed clinical psychologists will inform prospective participants about the study and provide them with a flyer. The clinical staff will then send a VA-encrypted e-mail containing the contact information of any interested Veterans to the study coordinator. A member of the research team (i.e., licensed physical therapist, licensed occupational therapist, or clinical psychology post-doctoral fellow) will follow up with interested Veterans in person to further discuss the study and obtain informed consent. Veterans will be explicitly informed that they can leave the study at any time without penalty and that they can participate in VR as part of their PT even if they choose not to consent for participation in the study.

The CPRP provides two daily group sessions of PT, each session containing up to six Veterans. Within each PT session, participants will be randomized into groups of three. One group will receive the VR intervention for the first 20 min with the other group receiving PT. During VR sessions, one participant will use the Oculus Rift and two participants will use Samsung Oculus Gear VR. During the first VR session, the intensity hierarchy will be explained, and Veterans will begin by using guided meditation (low intensity). In each session, the Veterans will be asked whether they wish to progress to a higher intensity VR APP or continue using similar intensity APPs and their preference to sit or stand during their VR participation. The Veteran will choose whether to sit or stand during their VR participation. After the 20-min VR sessions, the groups will switch treatment modalities (VR to PT and vice versa). Following each VR session, Veterans will be administered the daily rating form. Fear of movement and pain outcomes will be treatment progress measures administered to all Veterans by CPRP staff at admission and discharge. These research teams will retrieve these measures along with demographic information from the VA electronic medical record. Engagement between participants and the research team during VR sessions will help ensure adherence to the intervention protocol. A customizable user manual for Oculus Rift and Samsung Oculus Gear VR was developed for this study to assist in training the research team and to use with the study protocol (available upon request). The study schedule is presented in Table 2.

**Table 2 Tab2:** Study schedule

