### Analytic plan

All demographic characteristics, primary and secondary measures, will be described by the use of means and standard deviations for continuous variables and percentages for categorical variables. Multiple steps will be taken to handle missing data. Missing value patterns will be examined using Little’s Missing Completely at Random Test [61]. Missing data will be estimated using multiple imputations with demographic information and participant baseline scores on primary and secondary measures as predictors of missing items [62]. Up to 20% of missing data will be allowed for the proposed study based on evidence suggesting that standardized bias of mean changes is acceptable when using multiple imputation techniques in a small sample (*N* = 20) [63].

#### Aim 1

Describe the individual Veteran trajectories and APP intensity ratings across the proposed distraction-to-exposure hierarchy. Distributions of the Veteran-selected VR APPs (proposed movement intensity range of 1–6) will be calculated and plotted across all sessions over the course of the study. The frequency of individual Veteran trajectories will be counted to identify common patterns for the preferred level of movement. Veteran’s average self-reported intensity ratings for individual VR APPs will be plotted across sessions. Consistencies between the level of movement required to engage in the APP and self-reported intensity will be descriptively examined.

#### Aim 2

Estimate the within-subjects effect size and 95% CI for changes in fear of movement to provide insight into the likely magnitude of effect associated with the VR intervention. For the primary outcome (POQ-VA: fear of movement) the within-participant effect size calculations (*M*_post_ – *M*_pre_/SD_diff_) will be made along with 95% CIs to provide insight into the effect associated with VR utilization [64]. This step will also be completed for the FDAQ. Furthermore, the FDAQ mean difference from baseline and 95% CI will be calculated and compared to the established MCIC for this measure. The proportion of Veterans that experience clinically meaningful change will then be calculated. For secondary pain and functional measures, the effect sizes, mean differences from baseline with 95% CIs, and the proportion of participants that experience meaningful change will be examined. Data from secondary measures will be used to select optimal instruments for use with VR in a larger RCT.

#### Aim 3

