Examining the feasibility of this protocol will also be beneficial for Veterans, clinicians, and policymakers. Per the 2016 National Pain Strategy [67], the federal government’s first coordinated plan strives to reduce the burden of chronic pain in the USA. Variations in clinical practice and inadequate tailoring of pain therapies, as well as a reliance on relatively ineffective high-risk treatments, have contributed to the poor quality of care for people with pain [67]. If the aims of this research are achieved, VR will be used in combination with established pain management strategies to decrease pain and opioid use. VR has the advantage of being easily implemented both within VA healthcare settings as well as in Veterans’ own residences, where engagement in ongoing self-management approaches is often most challenging.

VR therapies are projected to have a $3.9 billion market size by 2023 [68], yet despite this tremendous public health burden, published research to date has not extended beyond pilot trials and case studies. Given the lack of large-scale RCTs examining the clinical effectiveness of VR, findings from the proposed study will present a key step to inform a larger RCT to validate our proposed hierarchy and compare it to an active control group (i.e., VR APPs with no known therapeutic value). This level of RCT evidence represents a necessary next step in the evolution of clinical VR research.

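### Aim 2 labels the admission-to-discharge change as the effect associated with VR, but it is the change during the whole CPRP with VR added, and it is then used to power the RCT

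*Protocol article*

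**What the plan says.** Under Aims and objective, Aim 2 estimates a within-subjects effect size with 95% CI "to provide insight into the likely magnitude of effect associated with the VR intervention". The Analytic plan repeats this reading for the primary outcome, the POQ-VA fear subscale: the mean change divided by the SD of the differences is calculated "along with 95% CIs to provide insight into the effect associated with VR utilization".

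The Design section sets out a single group: "Primary and secondary outcomes (Aim 2) will be assessed using a within-subjects pretest-posttest design". It also states that "The VR intervention will be implemented as an adjunct part of graded exposure physical therapy (PT) sessions in the CPRP". Under Procedures, the outcomes are "treatment progress measures administered to all Veterans by CPRP staff at admission and discharge", so the two measurements bracket the whole stay.

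The stay has other active content. Study setting describes a 19-day residential programme: "The interdisciplinary treatment provided in the CPRP utilizes a cognitive behavioral treatment approach that targets the physical and psychological impact of chronic pain". Participants and recruitment adds that Veterans must accept an opioid taper from admission where one applies.

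The Discussion says that the effect size for fear of movement will be used to power a larger RCT. It later describes that RCT as comparing the VR hierarchy with an active control made up of VR applications of no known therapeutic value.

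**The concern.** The pre-post change combines the CPRP, the physical therapy, any taper, VR, the passage of time and regression to the mean. Several of these are aimed at the same outcome as VR. The Background calls re-engagement in feared movement through exposure a primary goal of chronic pain rehabilitation. The FDAQ section reports that instrument's sensitivity to change after graded exposure physical therapy, with no mention of VR. A favourable Aim 2 result is thus plausible even if VR contributes little. No section of the article states this limit.

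The main harm lies in the next step. A within-group change, carried forward as if it belonged to VR, would be used to size a trial whose result is a difference between arms. If both arms of that trial receive the same background care, the part of the change due to that care appears in both and drops out of the contrast. The trial would then be too small by an amount that cannot be worked out from the pilot data.

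**Working it through.** **1. The plan's own figures.** The article gives no sample-size or power calculation. Its attrition figure reproduces: 105/705 = 14.89%. Applied to the enrolment cap of 20, this leaves 20 × (1 − 0.1489) = 17.0 Veterans.

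**2. What Aim 2 estimates.** The formula is read as d_z = (M_post − M_pre)/SD_diff. With one group and every component given over the same interval, the expected value of d_z is the sum of all contributions. Nothing in the planned data varies VR while holding the rest fixed, so the VR share could be anywhere from 0 to 100%.

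**3. What the 95% CI covers.** Noncentral-t intervals for d_z:

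| Observed d_z | n = 20 | n = 17 |
|---|---|---|
| 0.5 | 0.03 to 0.96 | −0.01 to 1.00 |
| 0.8 | 0.29 to 1.30 | 0.24 to 1.34 |

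These widths reflect sampling error alone. The co-interventions shift the centre, and the interval does not show that.

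**4. Consequence for the RCT.** The assumptions are mine, because the article states none: two-sided alpha 0.05, power 80%, the same SD of change in both arms, and observed effects of 0.5 or 0.8 as examples. With d the between-arm difference in SD_diff units,

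n per arm = 2 × (1.960 + 0.842)² / d²

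- d = 0.5: 15.70/0.25 = 62.8, so 63 per arm
- d = 0.8: 15.70/0.64 = 24.5, so 25 per arm

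If the true between-arm difference is a share s of the observed change, power at the planned n is Φ(s·d·√(n/2) − 1.96). For d = 0.5 and s = 0.75: 0.375 × √31.5 − 1.96 = 0.145, which gives 56%.

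| Share s | d = 0.5: power at 63 per arm | n per arm needed | d = 0.8: power at 25 per arm | n per arm needed |
|---|---|---|---|---|
| 75% | 56% | 112 | 56% | 44 |
| 50% | 29% | 252 | 29% | 99 |
| 25% | 10% | 1005 | 11% | 393 |

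**5. Could earlier CPRP Veterans supply the missing contrast?** Take 26 weeks at four discharges per week, about 104 earlier Veterans, and assume that their scores exist. In SD_diff units:

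- SE of the difference = √(1/20 + 1/104) = 0.244, half-width 1.96 × 0.244 = 0.48
- SE of the pilot change alone = √(1/20) = 0.224, half-width 0.44

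The comparison is only slightly less precise than the pilot mean, but that mean is itself imprecise. If VR added 0.2 (assumed), power to detect it would be about Φ(0.2/0.244 − 1.96) = Φ(−1.14) = 13%.

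**The case against.** The strongest defence is that this is a feasibility pilot and is written as one. The objective is to prepare an RCT, the design is openly named as pretest-posttest, VR is openly called an adjunct, and Aim 2 speaks of insight and association, not causation. The research questions ask only for within-subjects effect sizes after VR, which the design does estimate. Most of this stands: a one-arm pilot is a legitimate choice, and the fault is one of labelling. But cautious wording does not help once the Discussion uses the number to power a controlled comparison.

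Three stronger readings are tempting, and the article does not support them.

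- A reader might infer that a no-VR benchmark is already in the records and was overlooked. Routine collection at admission and discharge makes that possible. But the article does not say when any instrument came into use, and it reports only descriptive characteristics and attrition for the cohort of 705, with no discharge scores. A concurrent no-VR group is not assured either, since Veterans who decline consent may still use VR.
- A reader might put a percentage on the programme's share of the change. The article gives no CPRP effect size, so any such figure would be pure assumption.
- A reader might take the Discussion's statement that "VR will be used in combination with established pain management strategies to decrease pain and opioid use" as a claim that this pilot will show VR reduces opioid use. It is a forward-looking statement of purpose about a combination of treatments. Opioid use is collected only descriptively and no analysis of it is planned, so the sentence need not be removed on this ground.

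**Conclusion.** The point holds as one of attribution and of onward use. Aim 2 and the Analytic plan attach VR's name to a quantity that is change during CPRP with adjunctive VR. Its confidence interval does not express the uncertainty about VR's share, and the Discussion's plan to power the RCT on it would carry the misattribution forward.

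The size can only be illustrated. If 0.5 were observed and used, a trial of 63 per arm would have about 56%, 29% or 10% power instead of 80% when the true between-arm difference is 75%, 50% or 25% of it. This rests on the assumed alpha, power and equal SDs, and on the raw d_z being entered as the between-arm effect. The article says that the estimate will be used for powering but does not say how. The attribution conclusion does not depend on these assumptions.

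**What to change.** 1. In Aims and objective (Aim 2) and in the Analytic plan, call the quantity change during CPRP with adjunctive VR, and state that the VR share is not identifiable from this design. This costs two sentences.
2. In the Discussion, replace the plan to power the RCT on the pre-post effect size. Take the SD of change, attrition and compliance from the pilot, and justify the between-arm difference separately for the active control intended. This costs one sentence now and a reasoned target difference when the RCT is planned.
3. Optionally, where the record holds the same admission and discharge measures for earlier CPRP Veterans (the POQ-VA fear subscale is the likeliest), report their change beside the pilot's. Label it non-randomised context, and note that with n = 20 the half-width of about 0.48 SD_diff cannot isolate a small VR effect. This costs a chart extract and the ethics approval or waiver for it. Steps 1 and 2 do not depend on it.
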